### Statistical analysis

A detailed statistical analysis plan will be produced prior to analysis and agreed by the Trial Steering Committee (TSC). Descriptive analyses will examine the baseline characteristics of the treatment groups. The primary analysis will be the comparison of change in the BDI-II, conditional on baseline score, between the escitalopram and placebo group and between the nortriptyline and placebo group. As an exploratory analysis, we will provide an estimate of the difference in mean BDI-II score and 95% confidence intervals between the two active treatments. Secondary analysis will describe the number of participants experiencing adverse events on the Modified Toronto Side Effects Scale. A comparison between the escitalopram and nortriptyline arms for the following secondary outcomes will be made: motor examination (part III), the individual and combined part I and part II (motor and non-motor experiences), the motor complications part of the MDS-UPDRS (part IV) scores and their changes from baseline; of the clinical global impression (CGI) change in health score, the number of adverse events and of drop-outs; and all other secondary outcome measures. Secondary analyses will be performed for outcomes at 8 weeks and at 26 and 52 week and after withdrawal for those who have completed these assessments (blinded long term follow up with placebo group). Multivariate joint models will be used to explore the relationship between stopping treatment and the BDI-II.

Planned sensitivity analyses of different disease stages (Hoehn and Yahr stages), severity of depression (BDI-II categories of mild-moderate-severe), presence of anxiety and cognitive impairment will be performed. Further sensitivity analyses will be decided after the initial data analysis.

### Economic analysis

We will calculate the net monetary benefit (NMB) of (i) escitalopram plus standard psychological care, (ii) nortriptyline plus standard psychological care, and (iii) standard psychological care alone, to evaluate which of the three treatment options is the most cost-effective treatment of depression in PD. NMB will be calculated as the cost per quality adjusted life year (QALY) gained of each treatment option multiplied by a willingness to pay for a QALY gained. The primary analysis will be from a health and social care cost perspective and including participant data only, with secondary analyses including carer data. The analysis will use trial data only, and will report the NMB at 8 weeks, in line with the trial’s primary outcome measure, and at 52 weeks.

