### Objectives

The primary objective of this trial is to establish the clinical and cost-effectiveness of escitalopram and of nortriptyline at 8 weeks compared to placebo in the treatment of depression in PD, in addition to standard psychological care in the NHS.

The secondary objectives are to establish i) whether after one year of treatment parkinsonism has deteriorated less in patients with Parkinson’s disease with depression on nortriptyline than on placebo; ii) the difference in adverse reactions between escitalopram and nortriptyline; iii) the long-term (after one year of treatment) clinical effectiveness and cost-effectiveness of escitalopram and nortriptyline compared to placebo; iv) the clinical effectiveness of escitalopram and of nortriptyline compared to placebo on anxiety, cognition, overall function, and health-related quality of life; and v) whether after one year of treatment parkinsonism has deteriorated more in patients with Parkinson’s disease with depression on escitalopram than on placebo.

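### The stated formula for net monetary benefit (cost per QALY gained multiplied by willingness to pay) is not net monetary benefit and cannot serve as the cost-effectiveness rule

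*Protocol article*

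**What the plan says.** The formula stands in one sentence of the protocol article, Economic analysis: "NMB will be calculated as the cost per quality adjusted life year (QALY) gained of each treatment option multiplied by a willingness to pay".

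The same section fixes how the result is used. NMB is to be calculated for escitalopram plus standard psychological care, nortriptyline plus standard psychological care, and standard psychological care alone, "to evaluate which of the three treatment options is the most cost-effective treatment of depression in PD". The analysis "will report the NMB at 8 weeks, in line with the trial’s primary outcome measure, and at 52 weeks". NMB is the only economic decision measure named.

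The Objectives section gives this weight: "The primary objective of this trial is to establish the clinical and cost-effectiveness of escitalopram and of nortriptyline at 8 weeks compared to placebo". It also lists one-year cost-effectiveness as a secondary objective.

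No other part of the article defines NMB or corrects the sentence. The article gives no cost, QALY or willingness-to-pay figures, and does not say whether the ratio is taken within each arm or against standard care.

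**The concern.** Net monetary benefit puts health and cost on one monetary scale: QALYs are valued at the willingness to pay, and cost is then deducted. The threshold can therefore decide whether an extra gain is worth an extra cost. The published sentence instead takes a cost-effectiveness ratio and multiplies it by the threshold. Cost is in the numerator of a quantity called a benefit, and nothing is netted off.

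At stake is which of the three options is declared most cost-effective, at 8 weeks and at 52 weeks. This is a formula that the article states, and states wrongly. It is not a detail left to another document.

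**Working it through.** **Inputs.** From the Economic analysis section: the formula, the three options, and the 8-week and 52-week horizons. Costs (C), QALYs (Q) and willingness to pay (λ) are not given, so every figure for them below is an assumption made for illustration.

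**Formulas.**
- Stated rule: (C/Q) × λ, or (ΔC/ΔQ) × λ if incremental to standard care.
- Net monetary benefit: λQ − C. The difference between two options is λΔQ − ΔC.

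**Faults that hold on both readings.**
- Units: (money/QALY) × (money/QALY) = (money/QALY)², not money.
- λ multiplies every option's ratio equally, so no choice of λ changes the order.
- No cost is subtracted.

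**Reading 1: ratio within each arm, higher read as better.** Take C2 ≥ C1 > 0 and 0 < Q2 ≤ Q1, with at least one inequality strict. Then C2/Q2 > C1/Q1, so the stated rule always scores option 2 higher, while λQ2 − C2 < λQ1 − C1, so true NMB always scores it lower.

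Equal QALYs (0.75 each, λ = 20,000, costs 300 and 600):
- Stated: 300/0.75 × 20,000 = 8,000,000; 600/0.75 × 20,000 = 16,000,000.
- NMB: 0.75 × 20,000 − 300 = 14,700; 0.75 × 20,000 − 600 = 14,400.

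Unequal QALYs over one year:

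| Option | C | Q | Stated, λ = 20,000 | NMB, λ = 20,000 | Stated, λ = 30,000 | NMB, λ = 30,000 |
|---|---|---|---|---|---|---|
| Standard care | 2,000 | 0.60 | 66.7 million | 10,000 | 100.0 million | 16,000 |
| Cheaper, better | 1,800 | 0.65 | 55.4 million | 11,200 | 83.1 million | 17,700 |
| Costlier, worse | 2,500 | 0.55 | 90.9 million | 8,500 | 136.4 million | 14,000 |

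The order is exactly reversed at both thresholds.

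The 0.75 QALY example cannot occur at 8 weeks: with utility at most 1, an arm accrues at most 8/52 = 0.154 QALY. With an assumed mean utility of 0.65, 8 weeks gives 0.65 × 8/52 = 0.10 QALY. Costs of 300 and 600 then give 60 and 120 million by the stated rule, against NMB of 0.10 × 20,000 − 300 = 1,700 and 0.10 × 20,000 − 600 = 1,400. The reversal is the same.

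**Reading 2: ratio incremental to standard care.** For standard care alone, ΔC/ΔQ = 0/0, so one of the three required values does not exist. For the others, at λ = 20,000:

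| Option against standard care | ΔC | ΔQ | Stated | λΔQ − ΔC |
|---|---|---|---|---|
| Dominant | −200 | +0.05 | −80 million | +1,200 |
| Dominated | +500 | −0.05 | −200 million | −1,500 |
| Costlier, larger gain | +200 | +0.05 | +80 million | +800 |
| Costlier, smaller gain | +500 | +0.02 | +500 million | −100 |

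The first two rows share a sign although one is the best case and the other the worst. In the last two, the poorer option scores higher. At λ = 30,000 the last row's true value becomes 0.02 × 30,000 − 500 = +100. The threshold changes that decision, and the stated rule cannot show it.

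Instability: if utilities start equal and diverge linearly to an assumed difference of 0.05 at 8 weeks, ΔQ = ½ × 8/52 × 0.05 = 0.00385. With ΔC = 200, the stated rule gives 200/0.00385 × 20,000 ≈ +1,040 million. If ΔQ is −0.00385 it gives about −1,040 million. True incremental NMB moves only from 77 − 200 = −123 to −77 − 200 = −277.

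**The case against.** The sentence is probably a drafting slip. It names a standard quantity and mentions all of its ingredients: cost, QALYs and willingness to pay. The article condenses a fuller protocol, and nothing shown indicates that the operational plan repeats the slip. An analyst is unlikely to report squared money per QALY as a monetary benefit. The BDI-II outcome, the sample size and the clinical analysis are untouched. All of this stands. It bears on how likely harm is and how easy the repair is, but it does not make the stated formula correct.

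The article also never says that a higher value is better. That follows from the name of the measure, so the reversal on the per-arm reading is conditional on it. Reading lower as better does not rescue the rule, however. Take assumed options with C = 300, Q = 0.55 and C = 600, Q = 0.65, at λ = 20,000. The stated rule gives 10.9 and 18.5 million, so it would favour the first. True NMB is 10,700 and 12,400, which favours the second.

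Two stronger inferences are tempting, and the document does not support them. A reader might conclude that the rule always ranks a costlier, less effective option as better. That needs the per-arm ratio with higher read as better. On the incremental reading, an option that is costlier and less effective than standard care gets a negative value. A reader might also add all the faults together. The undefined reference option and the instability near zero belong only to the incremental reading, and the general reversal only to the per-arm one, so they are alternatives.

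**Conclusion.** Wrong as written. That conclusion is algebraic and needs no assumed figures: on either reading the stated quantity deducts no cost, is not in money and cannot respond to the threshold.

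The consequences depend on the reading. Per arm, with higher taken as better, the order is reversed whenever one option costs at least as much and yields no more QALYs (not equal on both). As an incremental ratio, the rule gives no value for standard care alone, cannot separate dominant from dominated options by sign, and is unstable when the QALY difference is small. The ceiling of 0.154 QALY per arm at 8 weeks makes a small difference plausible but does not prove it. The numerical examples rest entirely on assumed costs, utilities and thresholds.

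The error deserves correction because this is the sole named criterion for an economic question within the primary objective. A reader might infer that the trial's economic results will be wrong. The article does not show that; it shows only that the published definition is wrong, and that a correct later analysis would depart from it.

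**What to change.** Replace the defining sentence in the Economic analysis section with:

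> NMB for each option will be calculated as (mean QALYs × willingness to pay for a QALY) minus mean cost, and options will be compared by the difference in NMB, at 8 and 52 weeks.

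This gives a defined value for all three options, standard care alone included, and the difference between two options equals the incremental form λΔQ − ΔC. Check that the full protocol and any analysis plan covering the economic evaluation use the same definition.

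The cost is one sentence and a consistency check. Data collection, sample size, the clinical analysis and patient management do not change.

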### Internal Pilot study

The trial will include an internal pilot study in the first 6 months with the aim to recruit 46 participants. The results of this pilot study will determine progression to the full trial. Aggregated data will be collected on eligibility, uptake/recruitment, reasons for declining to participate where possible, adherence and attrition, as well as completion of outcome measures. The main progression criterion will be the ability to recruit, with additional consideration of rate of clinically significant adverse reactions, loss to follow up before primary outcome and adherence to trial medication through pill count.

### Patient and public involvement

The trial design and all patient-facing documents received extensive input from our Parkinson’s patient group. There is ongoing input on trial management and engagement from the group, including advice on trial procedures, engagement and dissemination of study information.

### Data management

Data management will be complete by the UCL Comprehensive Clinical Trials Unit. Data will be entered onto the ADepT-PD electronic database and monitored by the UCL comprehensive clinical trials unit. Data with personal information will be held coded and in a pseudo-anonymised fashion on a university network which is password protected. Adverse Events data will be coded using the Common Terminology Criteria for Adverse Events version 5.0. Range checks and data formats are checked on the electronic database. The database software provides a number of features to help maintain data quality, including maintaining an audit trail.

### Trial oversight

The UCL Comprehensive Clinical Trials Unit as the sponsor has overall responsibility for the trial, including site and investigator selection. The trial is overseen by the Trial Steering Committee which consists of external consultees from clinical, scientific backgrounds and people with lived experience of PD. The Independent Data Monitoring Committee whose members provide expert knowledge/advice on different aspects notably clinical expertise on depression in Parkinson disease, conduct of clinical trials and statistical analysis of trial data, meet at scheduled time points throughout the duration of the trial to review interim trial data and safety data.

## Discussion

Depressive symptoms are a common and disabling feature of Parkinson’s disease from the early disease stages with increasing prevalence with advancing disease [23]. However, at present, there is insufficient evidence to guide the most appropriate treatment. Optimisation of antiparkinsonian treatment with dopaminergic medication may improve depressive symptoms, and psychological treatments should also always be considered, but these approaches are often not sufficient or feasible. Previous trials have suggested improvement with a number of different antidepressants, but trials have been small and with inconsistent results, and there are concerns about adverse effects, including deterioration of parkinsonism and cognitive worsening with antidepressants [11, 24, 25]. Trial evidence is most favourable for tricyclics, resulting in some guidelines suggesting their preferential use, but concerns about adverse effects in un-selected populations often limit their use in routine clinical care. A commissioned call by the HTA therefore sought to establish a placebo-controlled trial of a tricyclic antidepressant and an SSRI in patients with depressive symptoms in patients with PD in addition to routine clinical care.

This trial, which will compare nortriptyline as well as escitalopram against placebo in their effectiveness for depressive symptoms in patients with PD, is set in a routine NHS setting across the UK, and therefore has the potential to change clinical practice based on real-life trial evidence. It will examine the effect on depressive symptoms, anxiety, capability and health-related quality of life in these patients over an 8 week period, with 12 months continuation to examine longer term effectiveness. In addition, it will also establish the safety of these medications in this population, in particular with regard to change of parkinsonism and change in cognitive scores. This is also of relevance as nortriptyline has been reported in a several pre-clinical models to attenuate alpha-synuclein aggregation, which underlies PD pathology [15]. The current trial therefore also provides the opportunity to examine the potential of this compound to change progression of motor symptoms, using detailed motor assessments during On-periods, and Off-periods where possible, as well as wearable sensors. These outcomes will be examined over the follow up period of 12 months.

A range of non-motor symptoms of PD will be examined, and adverse events studied systematically with a side effects scale in addition to standardised reporting. Furthermore a health economic evaluation will be performed to assess whether clinical effectiveness, if found, will also be translated into cost effectiveness.

## Data Availability

Not applicable. The trial results will be published in a peer reviewed journal and made available at the end of the trial. The Investigators will have access to the final trial dataset.

## Abbreviations

ADepT-PD: Antidepressant trial in Parkinson’s
BDI-II: Beck Depression Inventory-II
CGI: Clinical Global Impression
DSM V: Diagnostic and Statistical Manual of Mental Disorders, Fifth Edition
HTA: Health Technology Assessment
ICECAP-O: ICEpop CAPability measure for Older people
NMB: Net Monetary Benefit
MAO: Monoamine oxidase
MDS: Movement Disorder Society
MoCA: Montreal Cognitive Assessment
MDS-UPDRS: Movement Disorder Society Unified Parkinson’s Disease Rating Scale
NICE: National Institute for Health and Care Excellence
PD: Parkinson’s disease
QALY: Quality adjusted life year
REC: Research Ethics Committee
TCA: Tricyclic antidepressant
TSC: Trial Steering Committee
SSRI: Selective Serotonin Reuptake Inhibitor
